### Qualitative analysis

The study's qualitative material (i.e. focus groups, interviews, Application Manager notes) will be submitted to content analysis (Elo & Kyngäs, 2008), focusing on the manifest content. Deductive content analysis will be favored, allowing implementation barriers and facilitators identified to be categorized with an existing framework, while remaining open to emerging categories. Deductive content analysis allows categories to be compared at different periods, fitting with the study's longitudinal design (Vaismoradi et al., 2014). For this purpose, the Consolidated Framework for Implementation Research (CFIR) will be used (Damschroder et al., 2009). Analysis will involve three phases (Elo & Kyngäs, 2008): 1) preparation, when the analyst attempts to get a sense of the entire dataset through immersion in the data; 2) organizing, during which an unconstrained categorization matrix will be devised with the CFIR's constructs, and the data will be coded, accordingly. At this point, the qualitative data management software, Atlas.ti version 8, will be used to code and categorize the material; and 3) reporting, which involves presenting the described contents (meanings) of the categories and addressing trustworthiness (Elo & Kyngäs, 2008). A product of these analyses will be matrices of facilitators, barriers and potential solutions raised by patients and physicians, at each main qualitative data collection period, using the CFIR. These will allow for the tracking of categories over time (Damschroder et al., 2015), to help identify patterns.

For the cyclical small tests of change of the implementation strategy, consistent with the approach by Keith et al. (2017), the qualitative data will be coded and categorized with the CFIR. We will further structure and document our cyclical small tests of change by drawing on the iterative Plan-Do-Study-Act (PDSA) approach for quality improvement (Taylor et al., 2014). During the 'plan' stage, the stakeholder feedback collected will help to periodically identify and document factors that are affecting the intervention and associated changes to the implementation and/or peripheral components of the intervention that could lead to improvement. Related predictions will be explicitly articulated (Taylor et al., 2014). During the 'do' stage, changes will be tested. At the 'study' stage, the successfulness of the change will be evaluated against the prediction(s) and documented with subsequent qualitative or quantitative data, per the study's design, and the Application Manager's field notes. The

‘act’ stage will see further adaptations, depending on the successfulness of the change, and/or the initiation of another cycle of change. For each PDSA cycle undertaken, all decisions and relevant information will be recorded, following the PDSA theoretical framework developed by Taylor et al., (2014).

### Mixed methods analysis

The quantitative and qualitative data will be analyzed separately and subsequently brought together for comparison, for a more complete interpretation of the results. Areas of convergence and divergence will be highlighted.

### Participant security

#### Adverse events (AE’s)

An adverse event (AE) is any untoward medical occurrence in a patient-participant who is administered an intervention/treatment which does not necessarily have a causal relationship with this intervention/treatment. AE’s are therefore temporally related to participation in the study.

Participants in this study, whether they are involved in the interview or in filling out the study questionnaires, face no direct physical risk of participating as they will not be submitted to any pharmaceutical or invasive medical interventions. If an AE occurs in a patient who participated in this study, it is probable that it will involve a negative emotional reaction (e.g., distress, anxiety) caused by the qualitative interview about the intervention or by completing the I-Score PROM (e.g., on difficulties adhering to ART). Participants will be informed that they can be referred to a mental health professional within a reasonable amount of time should they experience significant emotional distress as a result of their participation in this study.

#### Documentation of AE’s

Any AE that occurs from the moment a participant signs the consent form to the time they leave the study will be documented by the study’s research personnel in the appropriate Case Report Form. The dates of the beginning and end of the AE, its severity (Grade), and the principal investigator’s judgment about the relationship of the AE to participation in the study (e.g., “definitely related” to “not related”) will be recorded on this form.

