### *Recruitment and consent process*

Physicians treating patients with HIV at the CVIS will be asked individually to participate, by oral or email invitation (see the Appendix for the email invitation). Patients of participating physicians will be recruited and consented in two ways: 1) when they visit the clinic; or 2) prior to an upcoming clinic visit. When they visit the clinic to meet with a health or social service provider (e.g., physician, nurse, social worker, psychologist), the provider will briefly describe the study. Alternatively, patients with upcoming visits will be identified and contacted to inform them of the study. If the individual agrees, the study coordinator will present the project in greater detail to them in person or over the phone, check the eligibility criteria, and obtain consent. Then, an appointment for a teleconference (on Zoom) will be made with the participant prior to their next regular clinic appointment with their physician to deliver training to use the app and complete the I-Score. Given efforts to limit in-hospital visits and risks for patients during the COVID-19 pandemic, in-clinic appointments with research staff will be avoided, when possible.

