### *The I-Score intervention*

During the study, participating patients will visit with their HIV physician three times, at Time 1 (T1), month 3 (T2), and month 6 (T3), prior to which they will complete the I-Score, as instructed. This visit schedule was selected as it fits within guidelines for the clinical follow-up of HIV in Quebec (Ministère de la santé et des services sociaux, 2019), while maximizing the collection of repeated study measurements. Given COVID-19, one visit (T2) will be done remotely (by phone or teleconferencing), while the other visits will be held at the CVIS. The I-Score PROM contains 20 items, covering 6 domains of barriers to ART adherence. Respondents indicate how often each barrier made adherence difficult in the past 4 weeks, with a continuous scale, from never to always. [Additional details on measure scoring and interpretation will be provided to the REB as they become available]. For details on the measure's development see Engler et al., 2018, Engler et al., 2019, Lessard et al., 2019, Toupin et al., 2018.

The core intervention of this pilot consists of having individuals with HIV on ART register on the Opal app and complete the I-Score PROM prior to each of three consecutive visits with their HIV physician. The patients will receive a reminder to complete the I-Score one week before their visit and they will have immediate access to their results. The HIV physician will acquire the I-Score results before each visit via the ORMS dashboard, an appointment and questionnaire management tool integrated with Opal and designed specifically for healthcare providers. The option of graphically presenting scores over time will also be available, allowing physicians and patients to compare past and present scores. It is expected that patients and physicians will review the I-Score results so they can be considered during the clinic visit (see Figure 1).

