### Obtaining consent

Both patients and physicians will receive an informed consent form to read (by email or in hand), to supplement the explanations provided by the research coordinator or study staff. To maintain distancing during the COVID-19 pandemic, remote consent will be favored. Both physicians and patients will have the option of printing, signing, and electronically returning the consent form (whether by taking a photo of or scanning the signed form). As physicians and some patients will be physically present at the CVIS for in-person medical appointments, they will be able to receive and sign a hardcopy of the ICF on site, prior to participation. For patients without a printer and not visiting the clinic prior to participation, oral consent will be possible, as this is a low-risk study for participants. This will involve having a third-party present when obtaining consent during a scheduled teleconference or phone conversation. Both the impartial witness and the person obtaining consent will sign the ICF. The ICF will be later signed by the participant at their next regular visit to the clinic (T0).

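### AE documentation starts at the participant's signature, which for orally consented patients comes after the first I-Score, so AE ascertainment differs by consent route

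*Protocol*

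**What the plan says.** Five places in the Protocol bear on this point.

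- Documentation of AE's sets the window for recording: "Any AE that occurs from the moment a participant signs the consent form to the time they leave the study".
- Adverse events (AE's) says that an AE, if one occurs, will probably be an emotional reaction "caused by the qualitative interview about the intervention or by completing the I-Score PROM".
- Obtaining consent provides a remote route: "For patients without a printer and not visiting the clinic prior to participation, oral consent will be possible". At that point "Both the impartial witness and the person obtaining consent will sign the ICF". The participant's own signature follows afterwards: "The ICF will be later signed by the participant at their next regular visit to the clinic (T0"). The label T0 is used nowhere else in the Protocol.
- Recruitment and consent process arranges a teleconference "prior to their next regular clinic appointment with their physician to deliver training to use the app and complete the I-Score".
- The I-Score intervention confirms the order for all visits: patients "complete the I-Score PROM prior to each of three consecutive visits with their HIV physician". It adds: "The patients will receive a reminder to complete the I-Score one week before their visit". Patients see their results immediately.

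**The concern.** The AE window is tied to an act by the participant, the signature. On the oral route that act is deferred to a clinic visit, and the study procedure that the protocol regards as a probable cause of distress is scheduled before that visit. Followed exactly, the rule does not require staff to document an AE that occurs between witnessed oral consent and signature.

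What is at stake is even ascertainment. A patient who signs before taking part has all three I-Score completions inside the window; an orally consented patient has two. AE records from the two groups would then not be comparable, and the gap falls on a procedure the protocol itself singles out. The oral route is a planned one: Obtaining consent favours remote consent, and the recruitment section seeks to avoid in-clinic appointments with research staff where possible.

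**Working it through.** The protocol gives no figure to reproduce. The check is to put the events in order for each consent route.

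| Step | Signs before taking part (electronic return or on site) | Consents orally |
|---|---|---|
| 1 | Participant signs; AE window opens | Witness and person obtaining consent sign; participant does not |
| 2 | Training and first I-Score | Training and first I-Score |
| 3 | First study visit | Next regular clinic visit; participant signs; AE window opens |
| 4 | Second and third I-Scores, interviews | Second and third I-Scores, interviews |

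**Could T0 be an earlier visit that closes the gap?** Oral consent is limited to patients who do not visit the clinic before participation, so the signing visit cannot come before participation begins. The consent section and the recruitment section both refer to the next regular clinic visit or appointment, and the rest of the protocol labels the first visit T1. T0 therefore appears to be the T1 visit, though the protocol does not say so.

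**Does another section open the window at oral consent?** No. Adverse events (AE's) describes AEs as related in time to study participation. That would include an event after oral consent, but it is a definition and sets no recording period. The recording rule is narrower than the definition.

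**Which named causes fall in the gap?** Two are named: the qualitative interview and the I-Score. Interviews take place only at T2 and T3, so on the stated schedule they follow the T1 signature. Only the first I-Score is affected.

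**Size.** Each orally consented patient has 1 of 3 I-Score completions before the window, or 33%. Across the study there are 30 × 3 = 90 scheduled completions. If k patients consent orally, k/90 of them are uncovered. The protocol does not give k, so these values are assumptions:

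- k = 0: 0/90 = 0%
- k = 10: 10/90 = 11%
- k = 15: 15/90 = 17%
- k = 30: 30/90 = 33%, the arithmetic ceiling

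The ceiling is not a realistic expectation. Oral consent needs both conditions (no printer, no prior clinic visit), and some patients are recruited and consented during clinic visits. Counting interviews as well lowers the share: a patient interviewed at both T2 and T3 has 3 + 2 = 5 exposures to a named cause, of which 1 (20%) is uncovered.

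**The case against.** The strongest reply is that this is a wording mismatch in a low-risk study, affecting a subgroup of unknown and possibly zero size. Much of that is fair, and it limits what can be concluded. Four stronger readings are tempting, and the protocol does not support them.

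- *A reader might infer that distress from the first I-Score can never be recorded.* The rule says when documentation is required; it does not forbid recording earlier events. Distress that persists or recurs after signature is inside the window, and the form captures start and end dates. Only an event that starts and resolves before the visit is outside the rule.
- *A reader might infer that the pilot's safety conclusion will be understated.* The objectives, the table of metrics and the analysis section contain no AE rate, safety endpoint or safety criterion for proceeding. There is no planned safety estimate to bias.
- *A reader might infer that the first I-Score is the exposure most likely to cause distress.* The protocol does not rank the first completion against later ones.
- *A reader might infer that, if T1 moves to a remote visit, signature slips to T3, since T2 is already remote.* Anticipated problems says only that adjustments may be needed and that the ethics board would be informed. The current schedule holds T1 at the clinic, and patients may also visit other clinic staff.

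It is also true that referral for distress is offered without any link to the AE form or to signature, so a patient's access to support does not depend on this rule.

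What stands after all this is the order of events. Nothing in the protocol opens the required window before the participant signs, and nothing places the signature of an orally consented patient before the first I-Score.

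**Conclusion.** The point holds in a limited form. For patients who consent orally, the required AE window opens after the first of three I-Score completions, so an emotional reaction that starts and resolves before the signing visit falls outside the documentation rule. Patients who sign beforehand are covered throughout. The result is incomplete AE ascertainment that depends on consent route.

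The size is one of three I-Score completions per affected patient; the study-wide share cannot be fixed because the number of oral consents is not stated. The conclusion assumes that the first I-Score is completed ahead of the visit, as the recruitment section describes, and that T0 means the T1 visit. No sample size, significance level, endpoint, test or progression threshold is affected. The text is worth correcting because a rule as written leaves out events that the protocol itself anticipates.

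**What to change.** In Documentation of AE's, start the recording period when consent is given, whether in writing or orally before a witness. For oral consent, take the start from the date of the signatures of the witness and the person obtaining consent, and make sure that date is entered on the form.

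In Obtaining consent, reconcile T0 with the visit schedule. It appears to be the T1 visit; the sponsor should confirm this and use one label throughout.

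The cost is one amended sentence and one label. No new procedure is needed, because those two people already sign at oral consent. The only downside is a slightly longer AE recording period for orally consented patients.

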### Expected study contributions

ePROM use for clinical practice with individuals living with HIV is limited. To our knowledge, this is the first pilot study of an intervention aimed at implementing systematic consideration of patient-identified ART adherence barriers with an ePROM in routine HIV care. This pilot study will help build needed knowledge on impediments to and strategies for implementing ePROMs in HIV care (Kall et al., 2020). As such, it acts as a standalone study, providing useful and rich data to others considering similar interventions in similar contexts. It will generate data that will improve understanding of conditions for successful implementation as well as test and solidify the implementation strategy. Furthermore, it may shed light on the mechanisms of ePROM interventions. Overall, it will produce useful data to design a definitive effectiveness trial of the I-Score intervention.

Conducted within a CIHR SPOR Mentorship Chair research program, awarded to the PI, [name], it will help train HIV researchers in patient-oriented research. The PROM initiative concerned by this study also challenges traditional care paradigms with a more patient-centered approach. It promises to shift an HIV treatment paradigm emphasizing biomedical markers (i.e. viral load) in adherence management. Systematic monitoring of patient-reported adherence barriers will allow for a more preventative approach and help ensure adherence management addresses patients’ priorities. The I-Score PROM includes only the most highly valued barriers in terms of relevance and importance to HIV care, as rated by people living with HIV in our Delphi consultation (Engler et al., 2019). As to the app through which the PROM is administered and its features, it may help redress the patient-provider knowledge imbalance and empower patients in their care (Rigby et al., 2015).

## Scientific contributions

### Communication of results and knowledge transfer

#### Scientific

The results derived from this study will be presented at national (e.g., Canadian Association for HIV Research) and international (e.g., Conference on Retroviruses and Opportunistic Infections; IAS Conference on HIV Pathogenesis, Treatment and Prevention) scientific conferences. We expect to publish up to four scientific articles in peer-reviewed journals included in common medical databases (e.g., PubMed, Medline). These will likely include: 1) a publication of the study's research protocol; 2) a publication of the quantitative data; 3) a publication of the qualitative data; 4) a publication of the mixed methods analysis. The targeted periodicals will be selected based on the nature of the manuscript and their potential to reach the desired audience.

#### Clinical

Presentations based on the project and its results will also be given to healthcare professionals working in HIV and its treatment (e.g., Chronic Viral Illness Service, Clinique Médicale L'Actuel, etc).

#### Community

We will present the results of the project at conferences that attract both HIV/AIDS associations and clinicians, particularly that of the *société française de lutte contre le sida* in France and that of the Canadian Association for HIV Research in Canada (CAHR/ACRV).

### Publication policy

The status of author for any publication produced in the course of this study will be attributed according to criteria of the « International Committee of Medical Journal Editors » (ICMJE). To be included as a co-author, the individual must have made a substantial contribution to these areas: 1) study conception, design or data collection, analysis or interpretation; 2) drafting the article or revising its main intellectual content; and 3) final approval of the version submitted for publication. The author must meet all three conditions, inclusively. Contributors who do not meet the criteria will be mentioned in the acknowledgements, where their particular contribution will be described.

Any source of funding for the study will be detailed in the area specified by the publication (e.g., conflicts of interests, acknowledgements) and in accordance with the funding body's requirements.

### Project timeline

The project timeline is presented in Figure 3. Broad milestones are as follows:

- January-February 2021: Physician and patient enrollment
- March 2021-August 2021: Data collection
- April 2021-October 2021: Data analysis
- September 2020-December 2021: Presentation and manuscript preparation (beginning with the protocol manuscript)

### Anticipated problems

There are many potential barriers to implementing PROMs in care, such as provider reticence (e.g., due to concerns for increased workload). Our multi-pronged implementation strategy directly seeks to mitigate numerous common barriers to implementing PROMs in care (Foster et al., 2018). For details, see Table 1.

Currently, physicians have been advised to use telemedicine and teleconsultations, whenever possible, to limit the spread of the disease (American Medical Association, 2020, Royal College of Physicians and Surgeons of Canada, 2020). Given the uncertain evolution of the COVID-19 pandemic and associated public health response, methodological adjustments to this study may be required to further limit in-person participant visits with physicians and research team members. The REB will be informed if this is the case.

## Project management

### Scientific committee

The pilot study team is multidisciplinary and has expertise in HIV clinical practice, biostatistics, trial design, health informatics, qualitative methods, psychometrics, epidemiology, PROM use for chronic disease management, implementation science, and HIV community concerns around treatment and adherence. The PI also has expertise in stakeholder engagement (e.g., Lessard et al., 2019), having notably been awarded a CIHR Mentorship Chair in patient-oriented research. With this Chair, all affiliated studies, prior to initiation, are submitted to a stakeholder committee with patient members for feedback (e.g., on study relevance, participation burden, data collection tools). These resources and competencies as well as a history of past collaboration between most team members will ensure the successful conduct and important contribution of this study. CTN funding for the pilot will allow us to secure matching funding for trainees through the MITACS Accelerate program, further ensuring the pilot's advancement.

## Ethical considerations

### Confidentiality

All the information collected about participants during the study will remain confidential as the law demands. To protect participant privacy, their information will be identified with an ID code of numbers and/or letters. Only the investigator in charge of the study will know the numbers and/or letters that link them to participants. Any study paper documents containing nominal information on the participants will be stored under lock and key and they will only be accessible to the project investigators and personnel. The questionnaires and audio recordings of the interviews will be identified by an alphanumeric code, assigned to each participant. All electronic files (e.g., interview transcriptions) will also be identified by a code and will require a password to access them. The computers used for analysis or record keeping will be protected by a password.

When the study is over, all study documents and data will be kept in a secure place at the Chronic Viral Illness Service of the McGill University Health Centre for 2 years. Afterwards, they will be archived at Iron Mountain in Laval, Quebec. Once the study's results have been published, it will be kept there for 7 years.

There are concerns for the collection of data on teleconferencing platforms such as Zoom for research with human participants. Care will therefore be taken to ensure confidentiality when configuring and recording the teleconference meeting. For example, teleconferences will require a password, and, when recording, "Local recording" will be 'on,' "Hosts can give participants the permission to record locally" will be 'off,' and "Cloud recording" will be 'off.'

